### Data management

Fieldwork supervisors will do daily quality checks on completeness of REDCap records on the tablets, before uploading data over 3G or Wi-Fi to the REDCap folder stored securely on the SAMRC’s server. A detailed description of the data management plan has been described elsewhere [21].

### Data analysis

The number of enrolled participants per SDPs over time and the number for whom 1- and 6-month outcome data are available will be presented. Throughout the analysis, outcomes will be disaggregated by HIV status and gender, which will be a covariate in analysis where sample size permits.

Analysis of 1-month and 6-month data (from questionnaires and routine data sources) will guide stratification and reporting by additional outcomes, such as proportion who took up the offer of immediate ART initiation at HIV diagnosis. Baseline characteristics of enrolled participants will be summarized by pre-/post-exposure status, to allow consideration of selection biases and lack of balance. The primary outcome will be modelled on SPD type using a logistic regression model and the standard errors of the estimated odds ratios will be adjusted for the clustering of participants within SDPs. Given the small number of clusters the degrees of freedom will be adjusted using the Between-Within method recommended by Li & Redden [32]. A time to event analysis will also be conducted for the time to ART initiation from the date of testing HIV positive, using a Cox regression model and adjusting the standard errors of the hazard ratio for the clustering of participants within SDPs. Demographic variables such as age and gender as well as barriers and facilitators of linkage to care will also be considered in the modelling process.

The process evaluation will be analysed through mixed methods. Linkage to care and retention in care will be expressed as proportions of the HIV-positive cohort. Characteristics of barriers and enablers to linkage to or retention in care will also be expressed as proportions and stratified by age and gender. A p-value of <0.05 will be considered statistically significant. A table shell is presented in S1 and S2 Tables.

Univariate analyses will also be used to describe the background characteristics of healthcare providers and health service readiness. Bivariate analysis will be done by cross-tabulating background characteristics of healthcare providers (age, education, job category, place of work, gender, and years employed) with the behavioural and organizational factors. Bar charts will be used to display bivariate analyses of key behavioural factors and organizational factors. A comparison between the different SDPs will be undertaken as well as an analysis to assess the effect of management support on the behavioural factors around health information. In addition to the above analyses, information from key informants on organisational determinants affecting the District Health Management Information Systems’ performance will be collated.

A general inductive approach, driven by the main questions of interest (e.g., barriers and facilitators of linkage to care), will be used to analyze the qualitative data. Two co-investigators (including the lead author) will read each translated transcript independently to gain a general understanding of its content and scope, and thereafter will develop a structured coding framework guided by the main questions of interest, as well as allowing for new concepts to emerge through open coding. The independent analyses will then be compared for consistency; areas of discrepancies will be identified through critical evaluation of the sets of themes. The source quotes will be reviewed and agreed upon, and a final thematic report will then be generated from the combined analyses. Through comparative analysis within and between interviews, we will develop categories of coded information which will then be linked to broader themes emerging across interviews. The same codes will be used to analyse the data within ATLAS.ti software and this will be used to compare and complement the manual analysis. Data from the qualitative interviews will be triangulated, where appropriate, with quantitative data emerging from the questionnaires.

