## Abstract

**Introduction:**

Adolescent girls and young women (AGYW) aged 15–24 years and adolescent boys and young men (ABYM) aged 15–34 years represent one of the populations at highest risk for HIV-infection in South Africa. The National Department of Health adopted the universal test and treat (UTT) strategy in 2016, resulting in increases in same-day antiretroviral therapy initiations and linkage to care. Monitoring progress towards attainment of South Africa’s 95-95-95 targets amongst AGYW and ABYM relies on high quality data to identify and address gaps in linkage to care. The aim of this study is to describe the current approaches for engaging AGYW and ABYM in the treatment continuum to generate knowledge that can guide efforts to improve linkage to, and retention in, HIV care among these populations in KwaZulu-Natal, South Africa.

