**Fig 1 pone.0271942.g001:**
[figure not shown]
An illustration of the study activities for the SHeS’Cap-Linkage study in uMgungundlovu district, KwaZulu-Natal, 2022.

Secondary data sources, including routine data from facility-based health information systems, routine data from district-level TIER.Net, data from the National Health Laboratory Service (NHLS) and data from the South African Medical Research Council (SAMRC)’s Rapid Mortality Surveillance (RMS) containing monthly information about deaths registered by the South African Department of Home Affairs will be used to obtain information on linkage to and retention in care in the SDPs where this project will be implemented. The RMS, therefore, will be used to confirm that the individual considered as not linked to care or not retained in care was not deceased. Table 4 gives an overview of the outcome variables, and data sources and tools.

**Table 4 pone.0271942.t004:** Roles of outcome variables in the SHeS’Cap-Linkage study in uMgungundlovu district, KwaZulu-Natal, 2021–2023.

Outcome variables	Examples of variables	Data sources and tools
• Proportion of AGYW and ABYM who have initiated ART as evidenced by a record in their TIER.Net within 14 days or for whom baseline CD4 results have been entered into their TIER.Net record within 1 month of their HIV-positive test result at enrollment. (Primary outcome)	• Patient receipt of HIV test result.	• Routine data (Clinical charts, clinic HIV testing and tracking registers, patient folders and TIER.Net*) and questionnaire data as necessary.
	• Patient attendance at first clinic appointment after receipt of HIV result.	
	• Enrolled patients taking up same-day initiation onto ART at diagnosis	
	• Proportion for whom ART initiation is within 2 weeks of a CD4 test	
	• ART initiation date recorded in clinical stationery and/or TIER.Net	
• Proportion of AGYW and ABYM for whom an entry has been captured into their TIER.Net record at 6 months after their positive HIV test at enrollment. (Primary outcome)	• Patient attendance at clinic as per contemporary NDoH guidelines at 6 months after HIV diagnosis	• Routine data (Clinical charts, clinic HIV testing and tracking registers, patient folders and TIER.Net*)
	• NHLS records of samples received at NHLS laboratory, as per contemporary NDoH guidelines (e.g., repeat CD4 or Viral Load results every 6 months)	• NHLS records
		• RMS
		• Baseline and follow-up questionnaires

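### The Cox model for time to ART has cluster-adjusted standard errors but no small-cluster correction on the same 22 SDPs, so its test rejects about 7–8% of the time at a nominal 5%; the handling of same-day starts at time zero also needs stating

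*Protocol article*

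**What the plan says.** All the relevant wording is in one paragraph of the protocol article's Data analysis section, in this order:

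1. "The primary outcome will be modelled on SPD type using a logistic regression model", with the standard errors of the odds ratios adjusted for clustering within SDPs.
2. "Given the small number of clusters the degrees of freedom will be adjusted using the Between-Within method".
3. A further analysis of "time to ART initiation from the date of testing HIV positive, using a Cox regression model and adjusting the standard errors of the hazard ratio"; here too the adjustment is for clustering by SDP.

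The third item repeats the cluster adjustment of the standard errors but not the degrees-of-freedom adjustment. The Abstract describes the Cox analysis in the same terms, again with clustered standard errors only. The Sampling section shows that the authors know the problem: it says that, with few clusters, service models should be compared at cluster level rather than participant level.

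On same-day starts, the Abstract describes the universal test and treat policy as "resulting in increases in same-day antiretroviral therapy initiations and linkage to care". Table 4 lists "Enrolled patients taking up same-day initiation onto ART at diagnosis" as a variable, and the Data analysis section plans to report the "proportion who took up the offer of immediate ART initiation at HIV diagnosis". The article gives no expected same-day share and does not say how a time of zero enters the Cox model.

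**The concern.** A cluster-robust variance is biased downwards when clusters are few, and a normal reference distribution ignores the uncertainty in that variance. Service model is a property of the SDP, so the information about it comes from 22 units, however many participants are enrolled. The article gives this reason for adjusting the logistic analysis. It applies equally to the Cox analysis, which uses the same clusters and the same exposure. As written, one of the two named regression analyses is protected and the other is not, and both are judged at p < 0.05. A borderline hazard ratio could be called significant beside an odds ratio that is not, purely because of the reference distribution.

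The second matter is the time scale. With a clock running from test date to ART date, a same-day starter has time 0. If the software excludes non-positive times, those records disappear from the time-to-event analysis although day 0 counts fully in the 14-day primary outcome. If service models differ mainly in same-day start, the hazard ratio could then disagree with the primary result.

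**Working it through.** **Inputs from the article.** 22 SDPs, 11 per model, 50 participants each, ICC 0.01, alpha 0.05, proportions 0.62 and 0.72 (Sampling; Table 2). The article states no figure for the Cox analysis, so there is none to reproduce. The only stated figure from these inputs is the power of 0.89 for two proportions. With design effect 1 + 49 × 0.01 = 1.49 it reproduces with one-sided alpha (0.895) but not two-sided (0.825). That is a separate matter and is not used below.

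**Part 1: small-cluster correction**

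- Between-cluster degrees of freedom for two models: 22 − 2 = 20 (19 if three models are compared).
- Two-sided 5% critical value: 2.086 on 20 df, against 1.960 for the normal. A robust z of 1.96 has p = 0.050 on the normal and p = 0.064 on t with 20 df.
- Null simulation of the Cox model with a cluster-robust variance, 11 + 11 clusters of 50, whole-day times, 14-day proportion 0.67 in both arms, same-day share about 0 or 40%, ICC 0.01 or 0.05, 3000 runs per setting:

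| Reference and variance | Rejection at nominal 5% |
|---|---|
| Robust SE, normal | 6.8% to 7.8% |
| Robust SE with K/(K−1), normal | 6.3% to 7.4% |
| Robust SE, t on 20 df | 5.6% to 6.6% |
| Robust SE with K/(K−2), t on 20 df | 4.7% to 5.6% |

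The simulation error at 5% is √(0.05 × 0.95/3000) = 0.4 percentage points, so the excess in the first row is not noise. Null simulations without ties, 4000 runs at each of four levels of cluster variation (SD 0 to 0.3 on the log-hazard scale), gave 7.3% to 8.2% uncorrected and 4.6% to 5.7% with the last row's correction. A further run gave 8.2% and 5.8%.

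**Part 2: time zero**

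The same-day shares s are assumptions. So is the use of 0.62 and 0.72 as proportions p started by day 14. If the hazard is constant from day 1 to day 14, the hazard ratio with day-0 records dropped is

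ln[(1 − p₂)/(1 − s₂)] / ln[(1 − p₁)/(1 − s₁)].

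- s = 0.30 vs 0.50: ln(0.28/0.50)/ln(0.38/0.70) = 0.95. On day 0 itself the ratio is ln(0.50)/ln(0.70) = 1.94; over days 0–14 as a whole it is ln(0.28)/ln(0.38) = 1.32. Day-0 records: 550 × 0.30 + 550 × 0.50 = 440 of 1100.
- s = 0.25 vs 0.55: ln(0.28/0.45)/ln(0.38/0.75) = 0.70.
- s = 0.40 vs 0.50: ln(0.28/0.50)/ln(0.38/0.60) = 1.27.
- s = 0.50 vs 0.50: ln(0.28/0.50)/ln(0.38/0.50) = 2.11.

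Dropping can therefore reverse the ratio, leave it nearly unchanged or inflate it, depending on the shares. If the arms differ only on day 0 (0.40 vs 0.60, equal hazard later), simulation gives 1.02 when day 0 is dropped, so the difference is lost. With day 0 kept it gives 1.35 (Efron ties) or 1.25 (Breslow ties).

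With records kept, the ratio depends on tie handling and on how long later starts are followed:

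- At 0.30 vs 0.50 and 0.25 vs 0.55, one set of simulations gave 1.30 to 1.34 with Efron and 1.22 to 1.25 with Breslow. An expected-count check shows that these match follow-up of about four weeks.
- In simulations that match follow-up of about six months, 0.40 vs 0.60 gave 1.18 (Efron) and 1.10 (Breslow), and 0.30 vs 0.60 gave 1.15 and 1.04.
- In the latter set Breslow fell below 1 only at the most extreme shares: 0.94 at 0.35 vs 0.65 and 0.93 at 0.20 vs 0.65. Efron stayed above 1 throughout.

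**The case against.** **On the correction.** The degrees-of-freedom sentence stands alone and gives a general reason, so it could be meant for every clustered model. The Cox model is an additional analysis in a study that calls itself exploratory, and the inflation is moderate. This bears on priority. It does not remove the point: the sentence follows the odds-ratio model, and the Cox sentence then restates its own variance treatment without the correction. A reader following the text would fit the Cox model uncorrected.

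**On time zero.** A reader might infer that the planned hazard ratio will lose or reverse the effect. The documents do not support that. The article never says that day-0 records are dropped, and zero times, ties and proportional-hazards checks are commonly left to a fuller plan. Reversal mainly requires dropping. Every same-day share used above is assumed; the article mentions increases in same-day starts but no number. The 0.62 and 0.72 are linkage rates, and linkage counts either ART or a captured CD4 result. They come from a power calculation tied to six months, so they are not 14-day ART starts. Nor are same-day starts lost from the study: the primary outcome includes day 0 and immediate uptake is reported separately. All of this stands, and it reduces the time-zero matter to a conditional clarification.

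**Conclusion.** The main point holds. As written, the Cox analysis lacks the small-cluster correction that the article puts beside the logistic model, and its test rejects about 7–8% of the time at a nominal 5%. This rests on 22 equal clusters of 50, two service models, a robust variance with a normal reference, and the range of between-cluster variation simulated. The effect is modest and matters for borderline results. Unequal cluster sizes were not examined.

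The time-zero point holds only conditionally: if the software drops zero times and same-day shares differ between service models, the difference can vanish or reverse. Its size cannot be fixed from the document. Replacing the single hazard ratio by a two-part model would be a preference, not the correction of an error.

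**What to change.** 1. Say in the Data analysis section that the small-cluster correction also covers the Cox model: a t reference on between-cluster degrees of freedom (about 20 for two models) with an inflated or bias-corrected robust variance.
2. Say that day-0 starts stay in the time-to-event analysis. One way is a small positive offset of less than one day with Efron ties; the Cox estimate depends only on the order of times, so the exact offset does not matter. Another is a discrete-time complementary log-log model that includes day 0.
3. Report same-day start by service model from the clustered logistic model beside the hazard ratio. Label any estimate from day 1 onward as conditional on not having started on day 0, and descriptive.

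**Cost.** A few words of analysis text and a few lines of code. Relative to an uncorrected robust interval, the interval on the log scale widens by (2.086/1.960) × √(22/20) = 1.064 × 1.049 = 1.12, about 12%. One more estimate is reported. No new data are needed, because same-day initiation is already listed in Table 4.

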### Ethics and dissemination

Ethical approval for this study was obtained from the South African Medical Research Council Health Research Ethics Committee (Ref #: EC052-11/2020) on 19 January 2021. Gatekeeper permissions were also obtained from the KwaZulu Natal Provincial Departments of Health (Ref #: KZ_202010_032), the uMgungundlovu health districts, and facilities. This project was also reviewed in accordance with CDC human research protection procedures and was determined to be research, but CDC investigators did not interact with human subjects or have access to identifiable data or specimens for research purposes. A waiver of parental consent has also been granted for participants aged 15–17 years, and documentation and informed consent process will be followed as for participants 18 years and older.

We will obtain oral and written informed consent from all potential participants in the study prior to their participation. Participation will be voluntary, and participants will be informed during recruitment that they could withdraw at any stage without consequences from the study team or the facilities which they attend. Any event deemed to be a serious adverse event (e.g., breach of participant confidentiality) will be systematically recorded and will follow the Standard Operating Procedures of the SAMRC Ethics Committee, which includes reporting adverse or unexpected events within 48 hours to the SAMRC Ethics Committee. Participation in the study may include disclosure of emotional and personal issues such as violence and stigma. Field staff will be trained on first-line response to disclosure of violence (LIVES) and will be capacitated to provide supportive referrals through the provision of a referral directory, should this be needed.

Dissemination of results will be extensive, both through scientific (publications and conference presentations) and through feedback and materials for the department of health, at facility, district, and national levels. The findings of the study will be presented to facility-based, district, provincial and national stakeholders, implementing partners, researchers in the scientific community and members of the public of South Africa, including participants attending primary care facilities in uMgungundlovu district. The anonymity and confidentiality of the participants will be preserved by not revealing any identifying information during the dissemination of study findings. Outputs will include a brief policy-relevant summary of findings, peer-reviewed journal articles, research capacity building through one or more research degrees, and materials to support enhanced capacity for scale-up of the interventions.

## Discussion

The aim of this study is to provide evidence to guide efforts to improve linkage to, and retention in HIV care among adolescent girls and boys, and young women and men in KwaZulu-Natal, in the context of the UTT strategy. Through UTT, HIV transmission can be reduced by early initiation to ART coupled with adherence to treatment. This suppresses serum concentration of the HIV virus (viral load count) in infected persons, reducing the risk of transmitting the virus to a negative person [17, 18, 33]. To attain the potential benefits of UTT strategies, those who test HIV-positive must be linked to care for treatment initiation immediately after testing, regardless of where they were tested [19]. Further, in order to achieve viral load suppression, all those on ART must be retained in care and adhere to lifelong ART [18]. This study has the potential to provide epidemiological data to further strengthen the HIV program in KwaZulu-Natal, and guide initiatives aimed at reaching the UNAIDS 95-95-95 targets.

The strengths of this study include the combination of research methods to answer the research questions. The study will combine data collected from people who take up HIV testing services and test HIV-positive with program monitoring through routine data to generate evidence to guide improvements in district and facility HIV services and ultimately to assist South Africa in reaching the UNAIDS 95-95-95 targets. The possible limitations of this study include the fact that we will be sampling adolescents which require the study team to be more sensitive and aware of their well-being during data collection as they might not be able to adequately express their health care service experiences. However, field staff will be trained on sensitive interview techniques and the provision of LIVES, to ensure adolescents feel safe and are able to disclose personal information. Other limitations have been described extensively in a complimentary study [21].
